### Outcomes

The primary outcome will be survival at 90 days. Secondary outcomes will be considered logistical, physiologic, as well as outcomes that will enable an economic analysis (a measure of utility and health-care costs). Logistical outcomes will include days free of (DFO) ICU, ventilation, renal replacement therapy, and hospital at 30 days from the index laparotomy. The physiological secondary outcomes will include change in APACHE II, SOFA, and ARDS scores after laparotomy. The COOL study inclusion criteria concerning intra-peritoneal contamination will be recorded, and the index source control laparotomy and every subsequent laparotomy will be graded according to the OA classification system from 2013 World Society of Abdominal Compartment Syndrome (WSACS) grading scale for OA [24, 56, 57]. Surgical complications occurring after the index laparotomy will be graded according to Clavien-Dindo (grade I = any deviation from normal postoperative course, including wound infections opened at the bedside but not treated with antibiotics; grade II = requiring pharmacological treatment, e.g., antibiotic treatment, blood transfusion, or parenteral nutrition; grade IIIa = requiring surgical, endoscopic, or radiologic intervention without general anesthesia and grade IIIb = under general anesthesia; grade IVa = life-threatening complication requiring IC/ICU management with single organ dysfunction and grade IVb = with multiorgan dysfunction; grade V = death of patient) [58, 59].

Bio-mediator outcomes for centers participating in COOL-Max will consist of the measurement of IL-6 and 10, procalcitonin, activated protein C (APC), high-mobility group box protein 1, C3a, C5a, and mitochondrial DNA. To enable a full economic analysis, we will measure 1-year health-care costs using administrative data and assess overall quality of life at 90 days and 1 year using the Euroqol EQ-5D standardized survey with translations into participants first language where necessary. An overview of the study outcomes is presented in Table 2.

**Table 2 Tab2:** Overview of study outcomes

	Indicator	Timeline
Primary outcome	Mortality	90 days
Secondary outcomes		
Logistical	Days free of ICU	30 days
	Days free of ventilation	30 days
	Days free of RRT^a^	30 days
	Days free of hospital	30 days
Physiological	APACHE II^b^ scores	Up to 30 days^c^
	SOFA^d^ scores	Up to 30 days^c^
	Pa0_2_/Fi0_2_^e^ ratios	Up to 30 days^c^
	ARDS^f^ scores	Up to 30 days^c^
Safety	Enterocutaneous fistula	30 days
	ACS^g^ and/or severe IAH^h^	30 days
	Intra-abdominal abscess	30 days
Biological	Il-6	Up to 30 days^i^
	IL-10	Up to 30 days^i^
	Procalcitonin	Up to 30 days^i^
	Activated protein C	Up to 30 days^i^
	High mobility group box protein 1	Up to 30 days^i^
	Mitochondrial DNA	Up to 30 days^i^
	C3a and C5a	Up to 30 days^i^
Microbiological	Intra-abdominal	Up to 30 days^j^
	Microbiological cultures	
Mass cytometry	Intra-peritoneal inflammatory cells	Up to 30 days^k^
Economic	Micro-costed resource consumption	1 year
Quality of life	Euroqol EQ-5D-5L	90 days and 1 year
	SF-36	90 days and 1 year

^a^*RRT* renal replacement therapy

^b^Acute Physiology and Chronic Health Evaluation Score

^c^Measured daily using the worst value of that day

^d^*SOFA* Sequential Organ Failure Assessment

^e^*Pa0*_*2*_*/Fi0*_*2*_ partial pressure of oxygen over inspired fraction of oxygen

^f^*ARDS* Acute Respiratory Distress Syndrome

^g^*ACS* Abdominal Compartment Syndrome

^h^*IAH* intraabdominal hypertension

^i^Measured as per Table 3

^j^Measured as clinically indicated by the treating team

^k^Measured on intra-peritoneal fluid obtained in Calgary

### COOL: COOL-Lite, COOL-Max, COOL-Mic, COOL-Cells, and COOL-Costs

The study will be powered to detect a mortality difference between the two allocated therapies which will be the most valuable deliverable of the study. Thus, any dedicated site can participate if they are committed to recruit and randomize patients with SCIAS fulfilling the eligibility criteria during source control laparotomies. Contributing towards this main outcome will require only collection of the clinical outcome data and is known as “COOL-Lite” participation in the study. Interested sites that have the capability to collect and store biological samples however will also be encouraged to participate in the “COOL-Max,” in which samples of both serum and peritoneal fluid will be collected to understand the evolution of bio-mediators in the course of SCIAS and to determine differential effects of open or closed abdominal therapy on these profiles. Participation in COOL-Max will involve collection of bio-mediator samples for a prior analysis as stipulated in Table 3. Participating in the COOL-Max effort will however equate to the collection of serum and peritoneal fluid which will be stored in a frozen state permitting other secondary and tertiary analyses correlated to COOL clinical outcomes in response to questions and avenues for scientific exploration as a result of this study. Other concurrent science that may be conducted in accordance with the main COOL trial will a COOL microbiology (COOL-Mic) arm that will consider the microbiology of secondary peritonitis in the OA arm of COOL-Lite and to follow the subsequent modifications in microbiologic flora including patients in the CLOSED arm who require reoperation; an analysis of the behavior of innate intra-peritoneal cellular defense mechanisms will be undertaken (COOL-Cells). Analysis of bio-mediator profile kinetics/dynamics will be on a “per-protocol basis” with per-protocol compliance requiring the delivery of at least 24 h of allocated treatment before any potential cross-over occurred regarding CLOSED or OPEN allocation.

**Table 3 Tab3:** Summarized bio-mediator samples for COOL-MAX centers

Will be drawn from both the serum and peritoneal fluid	
Timing of sample collection	
- Enrollment in the OR	
- 6 h post enrollment	
- 12 h post enrollment	
- 18 h post enrollment	
- 24 h post enrollment	
- 36 h post enrollment	
- 48 h post enrollment	
- 72 h post enrollment	
- 168 h (7 days) post enrollment	
- 336 h (14 days) post enrollment	
- 720 h (30 days) post enrollment	

For those patients recruited in Calgary (and potentially other geographically close sites in Alberta), mass cytometry specimens will be collected from the peritoneal fluid when possible (COOL-Cells). Mass cytometry is a mass spectrometry technique based on inductively coupled plasma mass spectrometry and time of flight mass spectrometry used for the determination of the properties of cells (cytometry). In this approach, antibodies are conjugated with isotopically pure elements, and these antibodies are used to label cellular proteins. Cells are nebulized and sent through an argon plasma, which ionizes the metal-conjugated antibodies. The metal signals are then analyzed by a time-of-flight mass spectrometer. The approach overcomes limitations of spectral overlap in flow cytometry by utilizing discrete isotopes as a reporter system instead of traditional fluorophores which have broad emission spectra. These sub-studies are not the focus of the present document, and COOL itself will be powered for survival considering the basic COOL-Lite protocol.

Finally, in COOL-Costs, we will use information on survival (which can be extrapolated to life expectancy), quality of life, and health-care costs to conduct a full economic evaluation. Overall quality of life will be assessed using the SF-36 and Euroqol EQ-5D-5L at 90 days and 1 year post-enrollment in survivors, either by paper or by phone, which has been used extensively in ICU survivors. The potential resource implications of the intervention include the cost of the strategy itself (which will be assessed using a microcosting approach) and include any implications on surgeries performed, ICU and hospital stay, any costs associated with adverse events of the treatment strategy, the costs associated with renal replacement therapy use after ICU discharge, and subsequent hospital readmissions. To measure these impacts, we will assess hospital and ICU length of stay, the number of surgeries performed (and types), physician interactions, and subsequent use of RRT for all patients within the trial, with valuation of all costs being based on all patients enrolled within Alberta, and other participating sites able to provide administrative and microcosting data. Microcosting data is available for all hospitalizations within sites in Alberta, which will enable an accurate evaluation of ICU costs separate from hospital ward costs—critical to this analysis. Additional health administrative data is also available in Alberta, including the ability to track all physician claims, and subsequent long-term dialysis use for study participants, using methods familiar to study investigators. For secondary analyses to inform policy makers in other countries, we will obtain similar costing information from additional participating countries to evaluate the cost-effectiveness in varying economic contexts and enable the broadest possible generalizability and policy relevance of our analysis.

### Participating centers

Participating institutions will be expected to be familiar with the proper utilization of the ANPPT device or else undergo an in service with a content matter expert on ANPTT device utilization prior to site participation. For both arms of the trial, it will be expected that attending surgeons are involved in either the direct supervision and/or inter-operative participation with either facial closure or temporary abdominal closure in order to be an acceptable participating center. Further criteria required for potential participating centers are presented in Table 4.

**Table 4 Tab4:** Site requirements for potential participation in the COOL study

Minimal system resources required for site participation in COOL-Lite	
- Designated primary investigator presumably with an academic affiliation willing to take overall medical/ethical/academic responsibility for the conduct of the study	
- Ethical approval—by the appropriate local ethics committee with oversight of the participating institution	
- Site investigators/willing local surgeons with the responsibility of caring for those with SIAS and thus the ability to recruit patients	
- Internet access—either within or closely available to the operating theater to allow online randomization of patients during laparotomy	
- Negative peritoneal pressure therapy (NPPT) dressing availability for those randomized to OPEN	
- Familiarity with the application of the NPPT device or willingness to undergo training and in service on the safe utilization of the NPPT device	
- Study personnel/investigator capable to record and compile case record and submit to the Central Study Registry	
Full system resources required for site participation in COOL-Max	
- Above and also	
- Study personnel capable of obtaining blood/IPF samples	
- Laboratory capability to store frozen blood/IPF fluid till study completion and send to Calgary for analysis	
Full system resources required for site participation in COOL-Mic	
- Medical microbiology laboratory capable of basic microbiology studies	
- Medical records and information processing capable of providing microbiology results for study analysis	
Full system resources required for site participation in COOL-Cells	
- Geographic proximity to Calgary	
- Ability to collect fresh peritoneal fluid and to rapidly ship to the Snyder laboratory for time-of-flight mass spectrometer	
Full system resources required for site participation in COOL-Costs	
- Ability to provide administrative and microcosting data	
- Ability to administrator SF-36 and Euroqol EQ-5D-5L at 90 days and 1 year post enrollment in all survivors	

### Sample size calculations

The COOL trial will overall be powered to detect a significant difference in the primary outcome, 90-day survival. While there is little solid data with which to integrate, the preceding peritoneal VAC study revealed an intention-to-treat 90-day mortality of 21.7% in the ABThera group versus 50.0% in the Barker’s vacuum pack group [HR, 0.32; 95% confidence interval (CI), 0.11–0.93; *P* = 0.04] [60]. This 30% reduction in mortality is likely too dramatic to expect to be practically replicated, and thus, a more conservative effective of 10% reduction in mortality would be appropriate. Thus, given a mortality rate of 33% in the general population of those with severe intra-abdominal sepsis, and considering a power of 80% and an alpha of 0.05, the number needed to recruit in each arm is 275 patients.

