## Methods/design

### Objective/aims

The aim of the study is to test the null hypothesis that there will be no difference in survival when an OA management strategy administering ANPPT is utilized compared to a primary fascial closure strategy in patients with SCIAS. The study will be designed as a prospective, single-blinded, multi-center, international RCT. A SPIRIT diagram overview of the trial is presented in Table 1. The complete protocol is available at https://coolstudy.ca/.

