Emergency department	
Hospital ward	
Intensive care unit	
Vasopressors required prior to randomization—no. (%)	
Hours from sepsis diagnosis to laparotomy, median (IQR)	

^a^IQR interquartile range

^b^Septic shock as defined by SESPS-3 guidelines [7]

^c^WSESSS [8]

^d^CPIRO [43]

^e^*GCS* Glasgow Coma Score

^f^Acute Physiology And Chronic Health Evaluation II

^g^*INR* international normalized ratio

^h^*SOFA* Sequential Assessment of Organ Failure [110]

^i^Charlson Comorbidity Index [111]

^j^*PRBC* packed red blood cells

^k^*FFP* fresh frozen plasma

There will be a single interim analysis planned after the recruitment of 275 patients, which will analyze the difference in 90-day mortality between allocated therapies. The COOL investigators appreciate the general reluctance to stop randomized trials early due to the benefit and due to the frequent over-estimating of treatment effects [61–63]. Despite this, it is possible that the COOL trial will be great over-powered as although the sample size calculations are based on the best outcome data from randomized trials of NPPT, this is still inferential as there is no previous relevant data with which to accurately guide such calculations. Thus, if a profoundly significant difference is found (*p* < 0.01), the trial will be stopped; otherwise, it will continue to full recruitment (Fig. 2).

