The investigators and the scientific community have extensively reviewed and critiqued the results of the preceding peritoneal VAC trial [90]. Methodologic concerns with the peritoneal VAC trial were that it enrolled quite heterogeneous patients with a wide range of ages and included traumatized patients with an exactly known time of injury and severe IAS patients in whom the timing of onset of severe disease was inexactly known. Thus, the COOL trial will focus on a less heterogeneous group of patients with intra-operatively confirmed SIAS in order to increase the signal to noise ratio. The Steering Group considers conducting the COOL trial to be a practical undertaking. With a projected total necessary recruitment of 550 patients and with an average institutional estimate of 10 such patients recruited per year, this projects to 28 actively engaged centers globally for 2 years. The initial expressed interest far exceeds this number of centers, and it is likely that many will be able to recruit many more than 10 per year. For example, at the Pilot Center, Foothills Hospital in Calgary, Canada, the group was extremely supportive with the similar recruitment process of the peritoneal VAC trial, in which out of 63 potentially eligible patients, 45 (71%) were recruited over 15 months [27], with reasons for non-recruitment including gynecological procedures and rescue laparotomies outside of a regular operating room.

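### If the primary test is two-sided at 0.05, as the no-difference null implies, 275 patients per arm give about 74% power for 33% versus 23% mortality, not the stated 80%; the sidedness is not stated

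*Protocol article*

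**What the plan says.** The section on sample size calculations in the protocol article sets the trial's size on 90-day survival. It cites the preceding vacuum trial, with 90-day mortality of 21.7% against 50.0%, and sets that effect aside: "This 30% reduction in mortality is likely too dramatic to expect to be practically replicated". In its place it adopts a smaller one: "a more conservative effective of 10% reduction in mortality would be appropriate". Control mortality is taken as 33%. The conclusion, with the remaining inputs, reads: "considering a power of 80% and an alpha of 0.05, the number needed to recruit in each arm is 275 patients".

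The total is carried into the Discussion, where the recruitment forecast begins "With a projected total necessary recruitment of 550 patients" and leads to the projected number of centres.

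The article prints neither the mortality expected in the OPEN arm nor whether alpha is one- or two-sided. The objective, under Objective/aims, is to "test the null hypothesis that there will be no difference in survival". The section describing COOL-Lite and the sub-studies also speaks of a mortality difference between the two therapies without a direction. So does the interim stopping rule under Statistical analyses.

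**The concern.** This is the only sample size calculation in the article, and it supports the primary outcome. It gives enough inputs to be recalculated, and the usual two-sided calculation does not return 275. Either the power at the planned effect is lower than stated, or the calculation used a one-sided test that the article does not mention and that does not fit its null hypothesis.

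At stake is the chance of missing the effect the trial was designed to find. If the test is two-sided, that chance is about 26% rather than 20%.

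**Working it through.** **Inputs.** Control mortality 33%, power 80%, alpha 0.05 and 275 per arm are printed under Sample size calculations. Allocation is 1:1.

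**Reading the 10%.** The same paragraph calls 50.0% − 21.7% = 28.3 points a 30% reduction, so it uses percentages for absolute differences. A relative 10% reduction (33% to 29.7%) would need about 3,100 per arm and is ruled out. The comparison is therefore p1 = 0.33 against p2 = 0.23. The 23% is derived, not printed.

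**Attempt to reproduce 275, two-sided 0.05.** Write p̄ = 0.28, z(α) = 1.960, z(β) = 0.8416.

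- Pooled variance: n = [z(α)·√(2p̄(1 − p̄)) + z(β)·√(p1(1 − p1) + p2(1 − p2))]² / (p1 − p2)² = [1.960 × 0.6350 + 0.8416 × 0.6310]² / 0.01 = 315.3, so 316 per arm.
- Unpooled variance: n = (1.960 + 0.8416)² × (0.33 × 0.67 + 0.23 × 0.77) / 0.01 = 312.5, so 313.
- Arcsine: 314.2, so 315.
- Pooled with continuity correction: 335.
- Time-to-event: hazard ratio ln 0.77 / ln 0.67 = 0.653. The Schoenfeld formula gives 173 events. At mean mortality 0.28 that is about 309 per arm. The Freedman formula gives about 318.

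None of these is 275. The lowest, 309, is 34 above it.

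**Attempt to reproduce 275, one-sided 0.05** (z(α) = 1.645).

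- Pooled: 249. Unpooled: 246.2, so 247.
- Pooled with continuity correction: 268.
- 249 inflated for an assumed 10% loss: 277 as n/(1 − 0.10), or 274 as n × 1.10. The article states no such loss.

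The one-sided route comes nearer, but it reaches 275 only with further inputs that the article does not give.

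**Power at 275 per arm, 33% against 23%, two-sided 0.05.** Standard error under the null: √(2 × 0.28 × 0.72 / 275) = 0.03829. Under the alternative: √((0.2211 + 0.1771) / 275) = 0.03805. Power = Φ[(0.10 − 1.960 × 0.03829) / 0.03805] = Φ(0.656) = 74.4%.

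| Method | Power at 275 per arm |
|---|---|
| Pooled z, two-sided | 74.4% |
| Unpooled z, two-sided | 74.8% |
| Chi-square without correction, by exact enumeration | 74.6% |
| Chi-square with continuity correction, by exact enumeration | 71.5% |
| Log-rank (Schoenfeld, 154 events) | 75.4% |
| Pooled z, one-sided 0.05 | 83.5% |

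**Difference detectable with 80% power.** Solving the pooled formula for p2 with n = 275 and p1 = 0.33 gives p2 = 22.3%, a difference of about 10.7 points.

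**The case against.** The strongest reply is that the article prints neither two-sided nor 23%. A one-sided 0.05 calculation with continuity correction gives 268, within 3% of 275, so the planners may have used a one-sided test and rounded up. This stands in part: the two-sided reading is an inference, and it cannot be said outright that 275 is a miscalculation. It does not rescue the paragraph. It needs two choices that are not stated and still does not yield 275. It would also set a one-directional test beside a no-difference null and a stopping rule without direction. The earlier open-versus-closed trial cited in the Background had a higher risk of death with the open abdomen, so harm is a live possibility.

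A second reply is that the shortfall is modest: about 6 points of power, or 0.7 points in the detectable difference. That is fair. The type I error of the final comparison is not affected.

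A reader might also infer three stronger points that the article does not support.

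- The remark that "it is possible that the COOL trial will be great over-powered" might seem to contradict the shortfall. It concerns uncertainty about the true effect. If mortality fell from 33% to 18%, 275 per arm would give about 98% power. Being short at 10 points and over-powered at a larger effect are compatible.
- The silence on losses before day 90 might seem an error. A condensed article may leave this to the full protocol, which it cites and which is not shown.
- One might guess which input was mis-entered. For example, 28% against 18%, two-sided, needs about 277. Nothing in the article mentions those rates.

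**Conclusion.** The point holds in conditional form. With a two-sided 0.05 test and 33% against 23% mortality, 80% power needs 316 per arm (313 to 335 across the two-proportion formulas). The planned 275 give about 74%, or 80% for a difference of about 10.7 points.

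This rests on two inferences: that the 10% is absolute, which is the only workable reading, and that the test is two-sided, which the null and the non-directional wording elsewhere imply. If the test were one-sided at 0.05, 275 would give more than 80% power (83.5% without continuity correction), but the conflict would then be with the stated null. On either reading the paragraph needs correction.

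**What to change.** State the sidedness of alpha in the sample size paragraph and restate the paragraph so that inputs and output agree. With a two-sided 0.05 test it would say that 550 patients give about 74% power for 90-day mortality of 33% against 23%, or 80% power for a difference of about 10.7 points (33% to 22.3%). Print the OPEN-arm mortality so that the absolute reading is explicit. If a one-sided test was intended, say so and reconcile it with the null under Objective/aims.

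The cost is a change of wording and a stated power about 6 points less favourable; recruitment need not change. If the sponsor wants a true 80% for the 10-point difference with a two-sided test, the number is 316 per arm (632 in total), which is 82 patients more than planned.

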### Statistical analyses

The effectiveness of randomization will be displayed through a detailed presentation of patient demographic characteristics as outlined in Table 5. The analysis of the primary outcome, mortality, will be on an intention-to-treat basis related to the allocation of initial intra-operative therapy. There will be a planned subgroup analysis of the actuarial mortality stratifying patients into those with and without the presence of septic shock (defined as Sepsis-3 Consensus Guidelines) during the first 48 h after onset of peritonitis (if known and 24 h before and 24 h after the first laparotomy if not known). Secondary outcomes are described in Table 2. For the comparison of health-care costs, we will use established methods to enable comparisons of mean costs, as these are easily interpretable and relevant to health-care payer. We will include the full cost of the intervention, as well as the hospital costs for the cost categories noted above (for both groups) and will use non-parametric bootstrap estimates to derive 95% confidence interval (95% CI) and mean cost differences between the treatment arms. We will use 1000 bias-corrected bootstrap replications (including sampling with replacement from the original data) to estimate the distribution of a sampling statistic to derive 95% confidence intervals. In sensitivity analyses, we will also use generalized linear models to compare total costs across groups, considering three family distributions (Gaussian, inverse Gaussian, and gamma) and specifying two link functions (identity and log).

**Table 5 Tab5:** Baseline demographic characteristics of the study patients

Male/female,	
Age, median (IQR^a^), years	
Septic shock^b^	
World Society of Emergency Surgery Sepsis Severity Score^c^	
Calgary PIRO Score^d^	
GCS^e^, median (IQR)	
APACHE II^f^, median (IQR)	
Arterial pH, mean (95% CI)	
Base deficit, median (IQR)	
Lactate, median (IQR)	
INR^g^, median (IQR)	
Temperature, mean (95% CI)	
APACHE-II score^f^, mean ± SDd	
SOFA score^h^, mean ± SDe	
Charlson Comorbidity Index score^i^, median (IQR)	
Worst physiologic measurements prior to randomization, median (IQR)	
Systolic blood pressure, mmHg	
Temperature (injured patients), °C	
Temperature (sepsis patients), °C	
pH	
Lactate, mmol/L	
Base deficit, mmol/L	
INR	
Fluid administration prior to randomization, median (IQR)	
PRBC^j^, units	
FFP^k^, units	
PRBC/FFP ratio	
Crystalloid, L	
Patient location prior to OR admission—no. (%)	
Emergency department	
Hospital ward	
Intensive care unit	
Vasopressors required prior to randomization—no. (%)	
Hours from sepsis diagnosis to laparotomy, median (IQR)	

^a^IQR interquartile range

^b^Septic shock as defined by SESPS-3 guidelines [7]

^c^WSESSS [8]

^d^CPIRO [43]

^e^*GCS* Glasgow Coma Score

^f^Acute Physiology And Chronic Health Evaluation II

^g^*INR* international normalized ratio

^h^*SOFA* Sequential Assessment of Organ Failure [110]

^i^Charlson Comorbidity Index [111]

^j^*PRBC* packed red blood cells

^k^*FFP* fresh frozen plasma

There will be a single interim analysis planned after the recruitment of 275 patients, which will analyze the difference in 90-day mortality between allocated therapies. The COOL investigators appreciate the general reluctance to stop randomized trials early due to the benefit and due to the frequent over-estimating of treatment effects [61–63]. Despite this, it is possible that the COOL trial will be great over-powered as although the sample size calculations are based on the best outcome data from randomized trials of NPPT, this is still inferential as there is no previous relevant data with which to accurately guide such calculations. Thus, if a profoundly significant difference is found (*p* < 0.01), the trial will be stopped; otherwise, it will continue to full recruitment (Fig. 2).

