**Methods:**

The Closed Or Open after Laparotomy (COOL) study will constitute a prospective randomized controlled trial that will randomly allocate eligible surgical patients intra-operatively to either formal closure of the fascia or use of the OA with application of an ANPTT dressing. Patients will be eligible if they have free uncontained intra-peritoneal contamination and physiologic derangements exemplified by septic shock OR a Predisposition-Infection-Response-Organ Dysfunction Score ≥ 3 or a World-Society-of-Emergency-Surgery-Sepsis-Severity-Score ≥ 8. The primary outcome will be 90-day survival. Secondary outcomes will be logistical, physiologic, safety, bio-mediators, microbiological, quality of life, and health-care costs. Secondary outcomes will include days free of ICU, ventilation, renal replacement therapy, and hospital at 30 days from the index laparotomy. Physiologic secondary outcomes will include changes in intensive care unit illness severity scores after laparotomy. Bio-mediator outcomes for participating centers will involve measurement of interleukin (IL)-6 and IL-10, procalcitonin, activated protein C (APC), high-mobility group box protein-1, complement factors, and mitochondrial DNA. Economic outcomes will comprise standard costing for utilization of health-care resources.

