### Inclusion/exclusion criteria

Potential patients will first be identified in the emergency departments, inpatient ward, and critical care units of the participating centers. Eligibility will then be confirmed in the operating room during the conduct and near completion of a laparotomy for source control. Patients will be eligible for inclusion if they have SCIAS, as operationally defined by the COOL trial (Fig. 1).

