**Fig. 1 Fig1:**
[figure not shown]
Inclusion criteria for COOL

The inclusion criteria are conceptually a two-part assessment to ascertain if patients clearly fulfill the definition of both severe and complicated IAS while undergoing source control laparotomy. Thus, during the laparotomy, it will become apparent to the operating surgical team that the peritonitis is complicated, which will be reproducibly demonstrated by uncontained or unconfined purulent, feculent, or enteric spillage. In addition to being complicated, the inclusion criteria require that patients have severe IAS. For the purpose of the COOL study, severe will be defined by any of septic shock as defined by Sepsis 3 Consensus Guidelines [7], a World Society of Emergency Surgery Sepsis Severity Score ≥ 8 [8], or a Calgary Predisposition-Infection-Response-Organ Dysfunction Score ≥ 3 [43]. An elaborated explanation of the thought processes and identification attributes of these criteria modeled on a trial population of SCIAS patients was previously published by the COOL investigators [44].

The qSOFA score was developed as a simple clinical tool to identify patients with suspected infection who were likely to have poor outcomes that did not rely on laboratory testing [7]. However, during modeling, the qSOFA actually had the lowest AUC of the systems formally tested and a lower identification rates than the other systems selected. This was consistent with other opinions that the qSOFA might not be a sensitive enough tool [45–48]. Therefore, although the qSOFA score ≥ 2 is not an inclusion criterion, its ease of use on the ward is attractive to serve as a flag for patients with IAS in whom caregivers should assess further whether critical features of SCIAS are present.

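### The septic-shock mortality subgroup is classified over a window that runs past randomisation, so membership can depend on treatment and its within-stratum comparisons can be biased

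*Protocol article*

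**What the plan says.** The Statistical analyses section of the protocol article states: "There will be a planned subgroup analysis of the actuarial mortality". The split is by presence of septic shock under the Sepsis-3 definition. The main classification window is "during the first 48 h after onset of peritonitis"; the alternative for patients whose onset time cannot be established is "if known and 24 h before and 24 h after the first laparotomy if not known".

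The time of allocation is given elsewhere. The abstract says the trial will "randomly allocate eligible surgical patients intra-operatively to either formal closure of the fascia" or the open abdomen. The Inclusion/exclusion criteria section adds: "Eligibility will then be confirmed in the operating room during the conduct and near completion of a laparotomy for source control".

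Shock status is also needed before allocation. Under the same eligibility section, "severe will be defined by any of septic shock as defined by Sepsis 3 Consensus Guidelines" or either of two severity scores. Septic shock is a row of Table 5, titled "Baseline demographic characteristics of the study patients", which also has a row for "Vasopressors required prior to randomization".

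**The concern.** A subgroup gives an unbiased treatment comparison only if membership is settled by information that allocation cannot affect. Here part of the classifying information is gathered after the abdomen has been closed or left open.

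The article itself expects treatment to act on early post-operative physiology. The abstract's rationale is that open management with active negative pressure will limit systemic injury, and post-laparotomy change in SOFA and APACHE II is a secondary outcome. All care after allocation is left to the clinical teams, who decide on re-opening a CLOSED abdomen and re-operating on an OPEN one.

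If OPEN prevents some new shock, patients who would have been in the shock stratum under CLOSED sit in the no-shock stratum under OPEN. The strata then differ in risk between arms before any effect on death is considered. The report could show a benefit or harm in patients with or without shock that is only an effect of sorting.

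**Working it through.** **Timing.** Take the end of the index laparotomy as roughly the time of randomisation.

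- Fallback rule (onset unknown): one day before and one day after the operation. The second day follows allocation in every such patient.
- Main rule (onset known): hours 0 to 48 from onset. If the operation ends t hours after onset, 48 − t hours follow allocation when t < 48, and none when t ≥ 48.
- Nothing in the article limits classification to data from before randomisation. It gives no distribution of onset-to-laparotomy times, so the share of patients affected is unknown.

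The article gives no size, power or expected effect for this subgroup, so there is no figure to reproduce.

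**Illustration with no true effect on death.** From the document: overall mortality 33% (Sample size calculations). All else is assumed. Three types of patient:

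- A: in shock before randomisation; share a, mortality mA = 45%.
- B: not in shock before, but in shock within 24 h under CLOSED; share b, mortality mB = 30%, 35% or 45%.
- C: never in shock under CLOSED; share c = 1 − a − b, mortality mC = (0.33 − a·mA − b·mB)/c.

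The pairs (a, b) were (30%, 20%), (40%, 15%), (30%, 30%) and (20%, 30%). OPEN multiplies the number of new shock cases by k.

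- CLOSED: shock stratum (a·mA + b·mB)/(a + b); no-shock stratum mC.
- OPEN, k ≤ 1: shock (a·mA + k·b·mB)/(a + k·b); no-shock ((1 − k)·b·mB + c·mC)/((1 − k)·b + c).
- OPEN, k > 1: the extra x = (k − 1)·b come from C, so shock (a·mA + b·mB + x·mC)/(a + b + x); no-shock stays at mC because the movers carry the average risk of C, a simplification.

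Spurious mortality difference, OPEN minus CLOSED, in percentage points:

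| k | Shock stratum | No-shock stratum |
|---|---|---|
| 0.5 | 0 to +2.6 | 0 to +8.2 |
| 0.7 | 0 to +1.3 | 0 to +5.5 |
| 1.0 | 0 | 0 |
| 1.5 | −1.4 to −6.0 | 0 |

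Worked cases, all with mB = 45%:

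- a = 30%, b = 20%, so mC = (0.33 − 0.135 − 0.09)/0.50 = 21%. With k = 0.5, no-shock mortality under OPEN is (0.10 × 0.45 + 0.50 × 0.21)/0.60 = 25%, against 21% under CLOSED: 4 points of apparent harm.
- a = 30%, b = 30%, so mC = (0.33 − 0.135 − 0.135)/0.40 = 15%. With k = 0.5, no-shock mortality under OPEN is (0.15 × 0.45 + 0.40 × 0.15)/0.55 = 23.2%, against 15%: +8.2 points.
- Same shares, k = 1.5: shock mortality under OPEN is (0.135 + 0.135 + 0.15 × 0.15)/0.75 = 39%, against 45%: −6.0 points.

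With membership fixed before randomisation, allocation cannot move anyone and every entry in the table is 0. For scale, the trial is designed around a 10-point difference.

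**Against sampling error.** In the +8.2 case, 275 per arm gives no-shock strata of about 110 CLOSED (40%) and 151 OPEN (55%). The standard error is √(0.15 × 0.85/110 + 0.232 × 0.768/151) ≈ 4.8 points, so the artefact is about 1.7 standard errors. Smaller artefacts are a correspondingly smaller fraction.

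**The case against.** The strongest reply is that this is one supportive subgroup. The primary analysis is intention-to-treat by initial allocation, and neither the sample size nor the interim rule uses the subgroup. That stands, and it limits the weight of the point.

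A second reply is that bias requires allocation to alter shock or its ascertainment. If it does not, the artefact is zero. Patients with known onset and an operation ending more than 48 h later are classified wholly before allocation. Both statements are right. They make the bias conditional, but they do not make the definition safe, because the condition cannot be verified in advance and the trial's rationale points to such an effect.

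A third reply is that the artefact may be small against noise. Suppose 50% are in shock at baseline (mortality 45%), 50% are not (mortality 21%), 15% of the latter develop shock, and OPEN labels a further 15% of them. Mortality in those never truly shocked is (0.21 − 0.15 × 0.45)/0.85 = 16.8%. Shock-stratum mortality is then 45.0% CLOSED and (50 × 0.45 + 7.5 × 0.45 + 7.5 × 0.168)/65 = 41.7% OPEN. That 3.3-point artefact (2.3 to 5.0 for 10% to 25% extra labelling) is about 0.6 of a standard error of 5.4 points, with about 158 and 179 patients. It would raise a nominal 5% false-positive rate to roughly 9%. This is fair for that scenario; the +8.2 case shows it is not a ceiling.

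Two related complaints do not hold. That the window differs with knowledge of onset makes the label less uniform, but knowledge of onset precedes randomisation and should balance between arms. The lack of a stated interaction test is no finding, since that detail may sit in the full protocol or analysis plan, neither of which is shown.

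**Conclusion.** The point holds in conditional form. The classification window always extends past randomisation in the fallback, and does so in the main rule when the laparotomy ends within 48 h of onset. Subgroup membership can therefore depend on treatment, and the within-stratum mortality comparisons can be biased.

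Under the assumed inputs the artefact runs from −6.0 to +8.2 points with no true effect on death. These figures show what is possible; they do not estimate what will happen. Only the 33% overall mortality comes from the document.

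A reader might infer that the subgroup result will be biased, that the error would favour the open abdomen in shock, or that the trial's main finding is compromised. The document supports none of these. Bias needs an effect of allocation on shock or its recording. Its direction depends on whether OPEN lowers or raises new shock, and the stated rationale, if true, gives an artefact against OPEN. The primary comparison does not use the subgroup. A reader might also take this as the trial's only subgroup, but that is known only for this article.

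It should be fixed before analysis; it is not a threat to the primary conclusion.

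**What to change.** Replace the two windows with one rule: the subgroup is Sepsis-3 septic shock present at or before randomisation. Preferably compare the treatment effect between strata with a treatment-by-baseline-shock interaction. Report shock arising after the operation as an outcome. If the wider window is kept for description, label that analysis exploratory and say that membership may be affected by allocation.

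The cost is about one sentence. Shock is already assessed for eligibility and is a Table 5 row; vasopressor use before randomisation is listed there too. Because patients can also qualify on a severity score alone, the text should say that shock status before randomisation is recorded for everyone, and the Table 5 row should carry the same time limit. The small downside is that patients first in shock after surgery move to the stratum without shock at baseline.
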